Compared to other developed regions of the world, the reported prevalence of obesity among adolescents in Nigeria is low however; this is rapidly increasing due to the corresponding rise in the behavioural antecedent risk factors specifically *unhealthy diets and physical inactivity*. A study by Odunaiya et al., (2010) among in-school adolescents in Oyo State, Nigeria found that, 38%, 58.8% and 3.2% engaged in low, moderate and high intensity physical activity behaviours respectively [12]. Furthermore, 8.8% were overweight and 1.2% were obese and body mass index was inversely associated with physical activity levels. Adeniyi et al. (2011) also found a significant level of physical inactivity among students in Ibadan, Oyo State and this was linked to individual and school factors [13]. According to Adeniyi et al, the physical activity levels of the participants varied; 53.8%, 38.8% and 7.4% engaged in low, moderate and high intensity physical activity behaviours respectively [13]. Physical inactivity was higher among students in private schools and associated with depression. The increasing level of physical inactivity in Nigeria and many other countries in the world is largely due to motorisation, urbanisation, automation of daily activities and greater opportunities for sedentary behaviours and underscores the need to address this growing burden [14–16].

In 2013, the World Health Assembly endorsed a resolution calling upon member states to address the needs of the youth by prioritising the surveillance of trends and determinants of non-communicable diseases and adopting a lifecourse approach in its prevention and control [17]. Evidence points to adolescence as a crucial period in the development of NCDs and underscores the need to institute or intensify surveillance of risk factors and implement population wide interventions to reduce the morbidity and mortality associated with these diseases. Schools have been identified as a setting for influencing the physical activity behaviours of young people but several factors influences its role in this regard. Numerous recommendations have been proposed to address physical inactivity and unhealthy diets within the school setting however; most of these strategies have targeted the individual level resulting in relatively modest changes in behaviours.

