## Methods

### Study research design

The proposed study will utilise a cluster randomised trial design to test the effect of a 12-week multi-level intervention on the physical activity and fitness levels of in-school adolescents aged 10–19 years in twenty two public and private-owned secondary schools in Oyo state, south western Nigeria. Secondary schools will be the unit of randomisation, and these will be assigned to the multi-level intervention or control arm (no intervention) with longitudinal data collection for index or cohort children randomly selected from the student population. Prior to the experimental study, preliminary data will be collected on the physical activity behaviours of in-school adolescents and the socio-ecological factors influencing the school physical activity environment. This will guide the design of a multi-level, multi-component intervention which will run for 12 weeks with assessments conducted at baseline, post-intervention and at 3-months follow-up. The design, conduct and reporting of this study will adhere to the Consolidated Standards of Reporting Trials (CONSORT) guidelines. Ethical approval was obtained from the Oyo State Research Ethical Review Committee (AD13/479/890) and permission from the Oyo State Ministry of Education. The trial is registered with the Pan African Clinical Trial Registry.

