### Study site

The study sites are Ibadan and Ogbomosho, urban cities located in Oyo State, the South-West geopolitical region of Nigeria. It is one of the three States carved out of the former Western region of Nigeria in 1976. Oyo State consists of 33 Local Government Areas. The State covers a total of 27,249 km^2^ of land mass and has a population of about 4.5million. The people of Oyo State may be divided into five broad groups which are: Ibadan, Ibarapa, Oyo, Oke-Ogun and Ogbomoso. The state has four universities, (one federal government university, a state government university and two private universities); four polytechnics (one state government owned and three private polytechnics) and over 500 public and private secondary schools (Fig. 1).

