### Blinding and sampling technique

Multistage sampling technique will be used for the study. Nigeria is divided into six regions with approximately six states each. The south west region was purposively selected for this study.Step 1:The study state was selected randomly from the six states in the south west region of Nigeria.Step 2:Two comparable Local Government Areas (LGAs) in the project state will be selected using simple balloting. The list of LGAs was stratified based on their socio-economic status and level of urbanisation. One of the LGAs will be the experimental while the other will serve as the control.Step 3:The list of schools will be obtained for the selected LGAs and stratified by ownership i.e. public and private and population size. Twenty two schools will be pair-matched based on their ownership (i.e. public and private) and population size and randomly allocated to either the experimental (11 schools) or control (11 schools) group by simple randomisation by an independent researcher not involved in the study.Step 4:The male and female student ratio for the selected schools will be obtained and used for the determination of students to be selected for each school disaggregated by sex. The selected in-school adolescents will serve as the index children though all the students in the schools allocated to the experimental group will be exposed to the intervention.Step 5:The number of arms for classes from each school will be documented and two arms of classes at each level in the school will be selected by balloting for the study.Step 6:Study participants in each class will be selected using systematic random sampling technique based on the male to female student ratio and expected cluster size for the school.Step 7:The selected respondents will be enrolled as a cohort in the experimental and control schools and followed up after the 12-week intervention.

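### Step 2 gives each arm one whole LGA, which contradicts the school-level randomisation of Step 3; if Step 2 is followed, arm cannot be separated from area

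*Protocol article*

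**What the plan says.** All of the allocation text is in the protocol article, Methods.

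- **Step 2** (Blinding and sampling technique): "Two comparable Local Government Areas (LGAs) in the project state will be selected using simple balloting", from a list stratified by socio-economic status and urbanisation. It then adds: "One of the LGAs will be the experimental while the other will serve as the control".
- **Step 3** (same section): "Twenty two schools will be pair-matched based on their ownership (i.e. public and private) and population size", and these are "randomly allocated to either the experimental (11 schools) or control (11 schools) group by simple randomisation", carried out by an independent researcher. LGA is not named as a matching factor.
- **Study research design**: "Secondary schools will be the unit of randomisation". The Abstract says the same.
- **Data management and statistical analysis**: the effect is tested with multilevel mixed models for repeated measures, with random effects for cities and schools.
- **Study site**: "The study sites are Ibadan and Ogbomosho, urban cities located in Oyo State". The article does not say whether the two LGAs correspond to these two cities.

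**The concern.** Step 2 fixes the arm at the level of the LGA. Step 3 fixes it at the level of the school. Both are stated outright in current text, so this is not a detail left to an analysis plan or a fuller protocol. Two teams working from this section could run two different studies.

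The difference matters. Under Step 3 there are 22 allocated units and a randomisation basis for the test. Under Step 2 there are two allocated units, one per arm, and the 11 schools in each are repeated observations on a single area. A change in one LGA during follow-up that has nothing to do with the intervention (a local policy, a facility, an event) would then be read as intervention effect. The study could still be reported as randomised by school.

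**Working it through.** The article states no figure that depends on this point, so there is none to reproduce.

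**1. Can both rules apply?** If the LGA fixes the arm, every school's arm is known once its LGA is known, and Step 3 allocates nothing. If schools are randomised, the Step 2 layout would arise only by rare chance. Assuming 11 schools per LGA:
- unrestricted 11:11 draw: 2 / C(22,11) = 2 / 705,432 = 0.0000028;
- every matched pair with one school in each LGA: 2 / 2^11 = 0.001.

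So the two steps describe different designs.

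**2. Are arm and LGA separable under Step 2?** Take the 22 schools with columns for intercept, arm and LGA. When arm equals LGA, the last two columns are identical, so the matrix has rank 2 with 3 columns. Only the sum of the arm effect and the area difference can be estimated. With one area per arm, no degrees of freedom remain to estimate area variation.

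**3. What does the baseline remove?** Write the arm contrast at follow-up as effect + stable area difference + area-specific change. Subtracting the T0 contrast removes the stable term. It leaves effect + area-specific change, which are aliased. A random effect for area does not help, because its variance cannot be estimated apart from the arm effect.

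**4. Illustration of size, under assumption.** From the article: control proportion 0.62, 500 students per arm, 11 schools per arm (500/11 = 45.45 per school), ICC 0.38. Assumed, because the article gives no value: an LGA-level SD (tau) of 3, 5 or 8 percentage points, and smaller ICCs of 0.05 and 0.10 for comparison. This models a single post-intervention comparison, not the planned repeated-measures model.

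- Design effect: DE = 1 + 44.45 × ICC = 3.22 (ICC 0.05), 5.45 (0.10), 17.89 (0.38).
- SE that the school-level test sees: sqrt(2 × 0.62 × 0.38 × DE / 500) = 0.055, 0.072, 0.130.
- True SD of the contrast when arm equals LGA: sqrt(SE² + 2 tau²).
- Rejection rate under a true null: 2 × P(T20 > 2.086 × SE / sqrt(SE² + 2 tau²)), with T20 a t variable on 20 degrees of freedom. At tau = 0 this returns 5%, as it should.

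| ICC | tau 3 points | tau 5 points | tau 8 points |
|---|---|---|---|
| 0.38 | 6% | 8% | 13% |
| 0.10 | 9% | 15% | 28% |
| 0.05 | 11% | 21% | 37% |

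Worked case: ICC 0.38 and tau 0.05 give sqrt(0.130² + 2 × 0.05²) = 0.148. The ratio is 1.139, the cut-off becomes 2.086 / 1.139 = 1.832, and the two-sided tail is 8%.

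**The case against.** The strongest reply is that the intent is clear. The Abstract, Study research design, Step 3 and Step 4 all treat the school as the allocated unit, and one sentence says otherwise. That stands, and it makes the confounding conditional on Step 2 being followed. It does not remove the contradiction.

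Three further replies have some force. The LGAs are chosen to be comparable, which should make area differences smaller, but one area per arm still leaves them inestimable. The cohort is measured at T0, T1 and T2, so constant differences can be removed. At the protocol's own ICC of 0.38 the illustrated inflation is modest, because the school-level variance is already large. The aliasing itself does not depend on the ICC.

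Stronger readings are tempting, and the document does not support them:

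- **That every area difference, including baseline activity, is counted as effect.** In a change-from-baseline comparison the stable part drops out.
- **That the article's own figures show how far the areas differ.** The Background gives 62.0% (58.8 + 3.2) moderately or highly active in one Oyo State study. In another, in Ibadan, "53.8%, 38.8% and 7.4% engaged in low, moderate and high intensity physical activity behaviours respectively", so 46.2% were moderately or highly active, a gap of 15.8 points. These are levels in two separate studies, not changes in two LGAs.
- **That the city random effect is aliased with arm.** This would follow only if the LGAs were the two cities, which is not stated.
- **That the study is non-randomised.** The LGAs are balloted, and how an LGA gets its arm is not described. The accurate criticism is one allocated unit per arm.

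**Conclusion.** Wrong as written: Steps 2 and 3 state incompatible allocation rules, and Step 2 also contradicts the declared unit of randomisation. If Step 2 is followed, the intervention effect cannot be separated from area-specific change between T0 and T2, and no analysis can repair this afterwards. If only Step 3 is carried out, the problem does not arise, so a reader should not infer that the trial is confounded whatever happens.

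The size cannot be fixed from the document, which gives no LGA variance. Under the stated assumptions, a nominal 5% school-level test would have a true error rate of about 6% to 13% at ICC 0.38 with an LGA-level SD of 3 to 8 points, and about 15% to 21% at ICC 0.05 to 0.10 with an SD of 5 points. The aliasing rests on no assumption beyond Step 2 being applied.

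**What to change.** Before allocation, delete the Step 2 sentence that assigns one LGA to each arm. The school-level randomisation of Step 3 then governs, and both arms can occur in both LGAs.

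Preferably, also state in Step 3 that matched pairs are formed within an LGA. If the school numbers allow complete pairs, LGA is then exactly balanced; with an odd number of schools in each LGA, one pair straddles and balance holds to within that pair. Without this, if all 11 pairs straddled the LGAs, a split of 8:3 or worse would occur with probability 2 × (1 + 11 + 55 + 165) / 2,048 = 22.7%. That would be chance imbalance rather than bias, so this part is an improvement and not a requirement.

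The cost is a change of wording, with no extra schools or students. The downside should be stated: experimental and control schools would share an LGA. Some activities under consideration (policy dialogue, advocacy with ministries, meetings with teachers) act above the school, so spill-over that pulls the estimate toward no effect is possible.

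If the arms have to stay in separate LGAs, the protocol should say so. It should then describe the study as a comparison of two areas with one allocated area per arm, not as a trial randomised by school, and limit the causal claim accordingly.

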### Data collection

The data collection will be at three time points the first will be at baseline (T0), the second will be immediately after the 12-week intervention (T1) while the third will be three months after the intervention (T2). Details in Table 1. The data collection will employ a mixed methods approach including:(i)A desk review of relevant state and national NCDs prevention policies and guidelines on physical activity and an assessment of the level of coherence of the School Health Promotion policy with these policies. Other documents which will be reviewed include the Physical Health Education curriculum and school timetable to assess the opportunities for PA during school hours. The policies which regulate the construction of schools will also be reviewed to assess the extent to which these documents regulates or influences the built environment and physical activity levels in school.(ii)Physical and Health Education Teachers will complete the School Physical Activity Policy Assessment tool (S-PAPA) – a standardised semi-structured tool which assesses physical education, recess and other physical activity opportunities before, during and after school [31]. For this study, only two components will be assessed - physical education and recess. Scores on the S-PAPA tool will be tabulated based on policies and practices identified as being related to children’s physical activity during school [32, 33]. Total point scores will also be either median-split into high- and low or stratified by percentile for analysis [34].(iii) Focus Group Discussions and In-depth interviews will be held with teachers and school principals respectively to assess their opinion about social norms and support and the extent of implementation of physical activity policies and programmes in schools, level of funding, and the frequency of engagement in structured physical activity. Observations will be conducted to document facilities for physical activity in the schools using the Sport, Physical Activity and Eating behaviour: Environmental Determinants in Young people (SPEEDY) checklist. The SPEEDY checklist measures the built environment of schools and can be scored to quantify environmental support for physical activity [35]. The checklist assesses school-level environmental variables such as *Walking Provision, Cycling Provision, Aesthetics, Sport and facility provision, Other facility and Design of the school grounds* [36] The scores from each of the key variables will be dichotomised into low and high based on percentiles, and the school physical activity suitability index will be computed [36, 37].(iv) A cross sectional survey will be conducted among the students using an adapted version of the *Physical Activity Questionnaire for Adolescents (PAQ-A)* [38] to generate self-reported data on the level of physical activity among young people. The PAQ-A is a self-administered, 7-day recall instrument. It was developed to assess general levels of physical activity for high school students approximately 13 to 19 years of age. It assesses the frequency of participation in physical activity during spare time, physical education period, lunchtime, after school, in the evenings and on weekends. A summary of the physical activity score is generated from the mean of 8 items, and ranges from 1 to 5, with higher scores indicating more frequent participation in physical activity [38]). The physical activity levels will be categorised into three; low physical activity level will be those who score between 1 to 1.9 while moderate and high physical activity levels will be those who score between 2 to 3.9 and 4 to 5 respectively [13]. For some statistical analyses, the self-reported physical activity level will be treated as a continuous variable. In a study to establish the convergent validity of the PAQ-A, the instrument was found to be significantly correlated to all self-report measures (including activity rating, *r* = 0.73; Leisure Time Exercise Questionnaire, *r* = 0.57; and 7-day physical activity recall interview, *r* = 0.59) [39]. The survey will also assess the frequency of engagement in structured physical activity from two time points (baseline and follow up) as the primary outcome measure. Based on the theory of Planned Behaviours which is the theoretical framework guiding this intervention, other variables which will be incorporated into the Physical Activity Questionnaire for Adolescents (PAQ-A) are the measures for attitude, subjective norms, perceived behavioural control and self-efficacy. A research tool which was theoretically derived by Motl et al., 2000 based on Theory of Reasoned Action (TRA) and Planned Behaviour (TPB) and Social-Cognitive Theory (SCT) will be used to assess the social-cognitive factors among this young people. This questionnaire has been tested and evidence provided for its factorial validity as a unidimensional measure of attitudes, subjective norms, perceived behavioural control and self-efficacy about physical activity among adolescent girls [40]. The core variables i.e. *knowledge of health benefits of physical activity, attitude, subjective norms, perceived behavioural control and self-efficacy about physical activity* will be analysed by scoring and summing up all question items and cut-offs will be determined using percentiles.The survey will be complemented with focus group discussions to assess their opinions about the individual, social, community, institutional and policy factors which influences the physical activity behaviours of young people.(v)Anthropometric and other physical measurements (body-mass-index for age, waist-to-hip ratio, blood pressure) will be documented. Anthropometric measurements will be taken twice and averaged; for discrepancy >10%, a third measurement will be taken. The height and weight will be assessed using standard anthropometric procedures. Height will be measured using a portable height meter/stadiometer. Students will be asked to take off their shoes and stand with their back to the portable height meter/stadiometer. The sliding bar will be lowered and pressed flat on the head and recorded to the nearest centimeter. Body weight will be measured using a digital scale and weight will be recorded to the nearest gram. Age -and sex -specific prevalence of overweight and obesity will be determined by the body-mass- index for age Z scores using the criteria defined by the World Health Organisation (WHO). According to the WHO cut off points; overweight is considered to be > + 1SD (equivalent to BMI 25 kg/m2 at 19 years), Obesity: > + 2SD (equivalent to BMI 30 kg/m2 at 19 years), Thinness: <-2SD, Severe thinness: < −3SD and Normal: > −1 to < +1 SD. Standard deviations (Z-scores) will be computed using the World Health Organisation (WHO) reference population, 2007 soft ware (Anthropometric Software Program, Version 1.0.4 [41]. Blood pressure will be measured and the mean of three measurements will be recorded. Referrals will be initiated for children whose blood pressure exceeds the 95th percentile for age. Waist circumference will be measured to the nearest 0.1 cm horizontally at the narrowest point between the lower end of the rib cage and iliac crest. Hip circumference will be measured to the nearest 0.1 cm, at the greatest horizontal circumference below the iliac crest at the level of greater trochanter. Waist hip ratio will be obtained as waist circumference/hip circumference.The fitness level of the adolescents will be measured using the 20-m shuttle run test (20-mSRT) also known as the multi-stage fitness test. The 20-mSRT is the most widely used field-based test for aerobic fitness in young people and UK percentile data and health-related cut points are available [42]. A systematic review recently concluded that the 20-mSRT is the most reliable and valid field based method to estimate aerobic fitness in young people [43]. Performance in the 20-mSRT is typically expressed as laps, levels or distance completed. The 20mSRT estimates the cardiorespiratory fitness (aerobic capacity). Children run back and forth between two lines 20-m apart following beep signals played from a pre-recorded CD. The pace of the test is ramped such that running speed increases by 0.5 km/h each minute or period. The test is finished when the child stops owing to fatigue or when he/she does not reach the line in time with the audio signal on two consecutive occasions [44]. The last completed run indicates the final result of the test. The physical fitness data will be analysed and used as continuous variables and an increase in test results will indicate higher physical fitness [45].(vi) Step count will be recorded using a pedometer. During the data collection process, 100 students (10% of the sample) will be asked to wear a Yamax SW200 Step Digi-Walker pedometer on their right hand for seven consecutive days, except during sleep and water based activities. Text messages/phone calls will be made daily as reminders to ensure compliance. The pedometers will be sealed with a sticker or cable to prevent reactivity i.e. a situation where individual change their normal activity pattern as a result of being monitored.The pedometers will be worn daily for seven days with a minimum of 4 valid days. Step counts of less than 1000 steps per day and greater than 30,000 steps per day will be treated as missing data [46]. Step count of 10,000 to 11,700 and over will be recorded as achieving the daily recommended levels of 60 min of MVPA in adolescents [47].

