### Reliability

To ascertain the reliability of the instrument, analysis of pre-test data will be done using Cronbach’s Alpha correlation coefficient of the IBM Statistical Package for Social Sciences (SPSS). A correlation coefficient greater than 0.7 will imply that the tool is reliable.

In order to ensure accurate and consistent measurements, the weighting scale will be calibrated with a known weight and the height scale will be checked and recalibrated daily before measurements commence.

Research assistants will be recruited and trained to assist in data collection and provision of support to students in completing the recall sections of the tools. Training sessions will include objectives of the study, importance of collecting accurate data and ethical issues. The questionnaire will be reviewed with them to ensure common understanding. They will be trained to relate skillfully and courteously with the respondents. At the end of the training session, the research assistants will role-play the administration of the questionnaires to demonstrate an understanding of the intricacies involved in data collection.

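### Arms are set by LGA and by school before students are sampled and enrolled, and nothing shown keeps the arm concealed until baseline is complete

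*Protocol article*

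**What the plan says.** The order is given in the protocol article, *Blinding and sampling technique*, as numbered steps.

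- Step 2, on the two LGAs: "One of the LGAs will be the experimental while the other will serve as the control".
- Step 3, on the 22 pair-matched schools: "randomly allocated to either the experimental (11 schools) or control (11 schools) group by simple randomisation by an independent researcher not involved in the study".
- Step 4 uses each school's sex ratio to fix how many boys and girls are taken.
- Step 5: "two arms of classes at each level in the school will be selected by balloting for the study".
- Step 6: "Study participants in each class will be selected using systematic random sampling technique".
- Step 7: "The selected respondents will be enrolled as a cohort in the experimental and control schools and followed up after the 12-week intervention".

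Self-reported activity is one of the two primary outcomes (*Primary outcome measurements*; *Data management and statistical analysis*). *Data collection* says of the instrument: "The PAQ-A is a self-administered, 7-day recall instrument". *Reliability* gives the research assistants, besides data collection, the task of "provision of support to students in completing the recall sections of the tools". The control arm receives no intervention (*Study research design*).

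**The concern.** Randomising schools balances the schools. It does not protect the make-up of the student cohort if students join after their school's arm is known. Those who agree, refuse or are replaced may then differ between arms in ways that the draw cannot correct.

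The self-reported outcome is exposed in a similar way. A student, or an assistant helping with recall items, who knows that the school will receive or has received an activity programme may answer or prompt differently from one in a school that receives nothing. This applies at T0 and at least as much at T1 and T2.

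The section's title promises blinding, but the only safeguard it gives is an independent person for the allocation. That protects the draw and not what follows it.

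**Working it through.** No figure in the article bears on this point, so there is nothing to reproduce. The check is of order and concealment, followed by an illustration on stated assumptions.

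**Does any other text place enrolment or T0 before allocation?**

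- *Study research design* puts preliminary data before the experimental study. It does not say that the cohort is enrolled, or T0 measured, before schools are allocated or told.
- *Intervention phase* has the cohort enrolled when the study begins, without relating this to allocation.
- The abstract and *Intervention phase* have baseline findings shape the intervention. This puts T0 before delivery, not before allocation.
- The CONSORT flowchart is not shown and cannot be used either way.

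The numbered order therefore stands. Step 7 also speaks of schools that already carry their arm.

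**Which routes remain open?**

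| Stage | Safeguard in the text | Still open |
|---|---|---|
| Choice of classes | Balloting | Little |
| Choice of students | Systematic random sampling to a sex ratio and cluster size | Little, short of subversion |
| Agreement, refusal, replacement | None stated | Yes |
| Assisted self-report at T0, T1, T2 | Assistants trained on accuracy; no masking stated | Yes |
| Location | Step 2 ties arm to LGA | Reveals the arm before any school draw |

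**Illustration of cohort make-up (assumed participation rates).** Input from *Sample size for the intervention study*: p = 62% active. Suppose everyone invited joins in control schools, while in experimental schools active students join at rate a and inactive students at rate i. The active share enrolled there is p·a / [p·a + (1 − p)·i].

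- a = 95%, i = 90%: 0.589 / (0.589 + 0.342) = 63.3%, a shift of +1.3 points.
- a = 90%, i = 80%: 0.558 / (0.558 + 0.304) = 64.7%, +2.7 points.
- a = 90%, i = 70%: 0.558 / (0.558 + 0.266) = 67.7%, +5.7 points.

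These are shifts in who is enrolled, not biases in the treatment effect. A shift that stays the same at T0 and follow-up largely cancels in a comparison of change.

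**Illustration of reporting (assumed).** If knowledge of arm moves a fraction m of the 38% low-activity students (100% − 62%) into the active category in one arm, the shift is 0.38 × m: 0.8, 1.9 or 3.8 points for m = 2%, 5% or 10%. Write b0 for this shift in the experimental arm at T0 and b1 for the shift at follow-up. The contribution to the difference in change is b1 − b0. Taking 1.9 points:

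- at T0 only: 0 − 1.9 = −1.9 (the gain is understated);
- at follow-up only: 1.9 − 0 = +1.9 (overstated);
- equally at both: 0.

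The sign depends on when the distortion occurs, and the article does not settle that.

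**The case against.** The best case for the plan has five parts.

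1. **Students are drawn by chance within balloted classes.** This stands. A reader might infer that staff who know the arm can hand-pick students. The text gives them no such discretion, so the enrolment concern is confined to agreement, refusal, replacement and subversion.
2. **The timing of consent and disclosure is not described.** This also stands. An article condenses the full protocol, consent pages are absent and an independent researcher could withhold the result. One cannot say that consent is in fact taken with the arm known. The written order permits it, however, and Step 2 makes the arm readable from location.
3. **The planned analysis uses T0.** *Data management and statistical analysis* tests the effect with multilevel mixed models for repeated measures. A stable imbalance at T0 would largely drop out. Differences in willingness or responsiveness, and reporting that changes between visits, would not.
4. **Assistants are not said to recruit, deliver the intervention or know the arm.** True. Their help with recall is nonetheless a contact point for the primary outcome, with no masking stated. Masking them at T1 and T2 may be unrealistic if facilities are refurbished and events run school-wide.
5. **Step count is a second primary outcome, from sealed pedometers.** It does not depend on assisted recall, but only 100 students wear one and their enrolment follows the same order.

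The content of the intervention is also not fixed at T0, which weakens the motive for arm-dependent answers then but does not remove it.

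**Conclusion.** The point holds as a correctable design weakness. As written, arms are set before students are enrolled and no shown text conceals them until T0 is complete. Participation and assisted self-report can therefore depend on arm. That is a possibility left open by the design, not a demonstrated bias.

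Its size and direction cannot be derived from the document, and the shifts shown above rest wholly on assumed rates. Two stronger readings are tempting and not supported:

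- A reader might express an enrolment shift as a share of the 10-point target difference (62% versus 72%). That would fit an unadjusted follow-up comparison, which is not the stated effect analysis.
- A reader might call T0 activity a contaminated adjustment covariate. The article treats it as one of the repeated measurements and does not name it as a covariate.

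The verdict rests on the numbered steps being chronological, as Step 7's wording suggests. If the unshown flowchart gives another order, the two must be reconciled.

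**What to change.** Reorder the steps and say so in *Blinding and sampling technique*:

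1. List the schools and pair-match them on ownership and population size. Both are known from the school lists, so matching needs nothing from students.
2. Ballot classes, sample and enrol students, and complete T0 in all 22 schools.
3. Only then have the independent researcher draw the allocation or, if it is already drawn, release it.
4. Reconcile Step 2 with Step 3. If arm follows LGA, decide and disclose which LGA is experimental only after T0. If schools are randomised within pairs irrespective of LGA, remove the LGA labelling. Without this, reordering conceals nothing.
5. At T1 and T2, state that questionnaire assistants take no part in delivering the intervention and, where feasible, are not told the arm. Where visible activities make masking infeasible, say so.
6. Report participation, refusals and replacements by arm.

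The cost is small. The steps, the staff and the independent researcher stay the same, and delivery already has to wait for baseline findings. The downside is that schools learn their arm later.
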